### Data management and monitoring

The data will be managed via the REDCap electronic data system [54, 55]. The research team based at University of York will enter the baseline data. Follow‐up data will be entered either by participants or by the research teams at the sites. Following data entry, data collected by paper questionnaire will be checked by another researcher based at University College London.

### Analysis

Data will be analysed in R Studio, with the alpha value set to 0.05. Outliers will be assessed and then handled based on clinically meaningful thresholds. This means only values that are unlikely to represent true clinical conditions are flagged. If outliers are retained in the analysis, sensitivity analysis will be performed to determine their impact on the results. Baseline characteristics will be reported by each arm using descriptive statistics: means and standard deviations (SDs) for continuous numeric variables [unless skewed, in which case the median and the interquartile range (IQR) will be reported instead]; and frequencies and percentages for categorical variables. Numeric variables include most recent diagnosis and acute events. All other variables are treated as categorical.

#### Primary analysis

The effect of treatment on the primary outcome (CO‐verified 7‐day abstinence rates at the 6‐month follow‐up) will be analysed by a mixed‐effect (multilevel) logistic regression model with fixed treatment and a random intercept for site, included to allow for any site‐level variation in treatment effect. We will employ a likelihood ratio (LR) test to assess the significance of including the random site effects by comparing the mixed‐effects model with a model including only fixed effects. In addition, we will calculate the intraclass correlation coefficient (ICC) to quantify the proportion of variance in the primary outcome attributable to differences among clinical sites.

Secondary outcomes at the 1‐ and 6‐month follow‐ups will also be analysed as described above if they are binary, or with mixed effects (multilevel) linear regression adjusting for site‐level variation if they are continuous numeric variables. Mean difference will be reported. For regressions, we will check the assumptions of normality of the residuals.

We will use a repeated measures analyses to examine changes in cigarette consumption (a reduction of ≥50%) and mental health symptoms across baseline, and the 1‐and 6‐month follow‐ups. For continuous mental health symptom scores, we will use a multilevel linear regression model. We will verify the assumptions of normality and homoscedasticity of the residuals using quantile–quantile (QQ) plots and residual versus fitted plots. If these assumptions are not met, we will apply appropriate transformations (e.g. log transformation for positively skewed data). For the binary outcome of a ≥50% reduction in cigarette consumption, we will use a mixed‐effects logistic regression model. We will assess for overdispersion by comparing the residual deviance with the degrees of freedom and will consider alternative models, such as negative binomial regression, if overdispersion is present. Our models will incorporate fixed effects for the intervention group, time (treated as a categorical factor) and their interaction to assess differential changes between groups over time. To account for individual variability, we will include random intercepts for each participant and clinic site.

Analyses of smoking‐related outcomes will follow the intention‐to‐treat principle. This means that all participants will be analysed in the groups to which they were originally assigned, regardless of whether they completed the study or adhered to the intervention. Following the Russell Standard [30], those participants who will be lost to follow‐up or who do not provide outcome data will be treated as people who smoke in the analysis. If the missing data mechanism is suspected to be missing at random (MAR), sensitivity analyses will be performed using multiple imputation and the last observation carried forward. MAR will be determined if significant differences are found between missing and observed data. If there are substantial changes in the results under different missingness assumptions this will also indicate MAR. A complete case and as‐treated analysis will also be conducted. The latter of which accounts for the fact that some in the control group may have used e‐cigarettes during the treatment period. In the event of a non‐significant difference between groups on primary and other outcomes, associated Bayes factors will be calculated using the method of Dienes to differentiate between evidence for no effect and data insensitivity [56], using the effect size from the sample size calculation as a prior and specifying a half‐normal distribution.

Two subgroup analyses will be conducted. The first to assess differences as a function of trust versus GP practice and the second to assess the impact of the change made in month 7 to the mode of delivery in the intervention arm. We do not pre‐specify subgroup analysis by severity of mental illness because of likely low recruitment of this population and associated limited power to detect effects.

There are challenges with achieving an appropriate sample size in studies recruiting vulnerable subpopulations. Thus, in a scenario where the sample size is not obtained, we plan a full Bayesian analysis. We will use Bayesian logistic regression to analyse the primary outcome of CO‐verified 7‐day abstinence rates at the 6‐month follow‐up. We will incorporate prior information from the feasibility study/sample size parameters into the model by using informative priors. Sensitivity analyses will be performed to assess the impact of different prior distributions. Instead of *P*‐values, we will focus on the posterior probability that the intervention is effective (e.g. the probability that the intervention reduces smoking rates) and report credible intervals.

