### Sample size

We aim to recruit 616 participants, with 308 participants asigned to each group. Pooling the results of the only three RCTs comparing e‐cigarettes with placebo e‐cigarettes [15, 35, 36] yielded an expected effect size of risk ratio (RR) = 2.01 for 6‐month abstinence rates. We consider this estimate to be conservative as most of these trials used older, less effective first‐generation e‐cigarettes. In fact, recently published trials comparing active treatment (NRT) with a modern third‐generation e‐cigarette in the context of stop‐smoking services [12] found a superior effect of e‐cigarettes on 6‐month abstinence rates of RR = 1.63. Based on established effect estimates for NRT versus placebo from high‐quality trials [37], findings from this trial therefore indirectly suggest that, compared with placebo/usual care, third‐generation e‐cigarettes (as will be used in this trial) may increase 6‐month abstinence rates by nearly threefold (RR = 2.62). Given the low abstinence rates in the control conditions observed in the feasibility study [26], we revised the expected abstinence rates in the control (standard care) group from 7.7% (based on previous trials with people with mental illness) [38, 39] to 5.0%. Based on the feasibility study results (finding an absolute risk difference of 9.5%) [26] and the fact that a modern e‐cigarette is used, we assume an effect estimate of RR = 2.62, as found in more recent trials, to be most appropriate. We therefore expect an absolute predicted risk difference of 8.1%, assuming 6‐month abstinence rates of 5% in the control group and 13.1% in the intervention (e‐cigarette) group. A sample of 616 participants (308 per group) would provide more than 90% power to detect this effect, with an alpha level of 0.05 in two‐tailed analysis. This sample size would also provide 80% power to detect a more conservative effect of RR = 2.32 (intermediary between effect estimates from older and effect estimates from more recent trials using modern e‐cigarettes), with an absolute predicted risk difference of 6.6% at the 6‐month follow‐up (5.0% for the control group vs 11.6% for the treatment group).

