#### Baseline measures

We will record age, sex, employment status, ethnicity, education, accommodation type and marital status (Table 2), as well as most recent diagnosis and acute events (e.g. hospitalization) in the last year based on the participants' medical records. We will also assess nicotine dependence with the Strength of Urges to Smoke Scale [47] and motivation to quit with the Motivation to Stop Scale [48]. Age started smoking, smoking duration, past year quit attempts, current use of tobacco products other than cigarettes and ever e‐cigarette use as a smoking cessation aid will also be recorded. Alcohol use will be measured using the Alcohol use disorders identification test for consumption (AUDIT‐C) [49]. Physical activity (strength training; moderate or vigorous aerobic physical activity) will be assessed with questions from the Allied Dunbar National Fitness survey [50]. Consumption of at least five portions of fruit and vegetables (Healthy Eating Index) [51] will also be recorded.

**TABLE 2 add70115-tbl-0002:** Measures of participant sociodemographic characteristics.

Characteristic	Question	Answer options
Age	What is your age?	18–99 years
Gender	What is your gender?	(i) Male (ii) Female (iii) Other
Ethnicity	How would you describe your ethnic background?	(i) White (ii) Mixed/Multiple (iii) Asian/Asian British (iv) Black/African/Caribbean/Black (v) British (vi) Chinese (vii) Arab (viii) Other
Education	What is your highest educational qualification?	(i) GCSE/O‐level/CSE (ii) Vocational qualification (iii) A‐level or equivalent (iv) Bachelor’s degree or equivalent (v) Master’s/PhD or equivalent (vi) No formal qualifications (vii) Other
Employment status	How would you describe your employment status?	(i) Employed full‐time (ii) Employed part‐time (iii) Self‐employed (iv) Retired (v) Student (vi) Voluntary worker (vii) Not employed but seeking work (viii) Not employed but not seeking work because of ill health (ix) Not employed but not seeking work for other reason (x) Other
Accommodation type	What is your current accommodation type?	(i) Purchasing with a mortgage (ii) Owned outright (iii) Rented from the local authority (iv) Rented from a private landlord (v) Rented from a housing association/trust (vi) Other
Marital status	What is your marital status?	(i) Single (ii) Married (iii) Living with partner/cohabiting (iv) Divorced/separated (v) Widowed (vi) Other

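### The primary model is valid but uses none of the prognostic baseline measures already collected; prespecifying two of them would be a cheap, modest improvement

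*Protocol article*

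**What the plan says.** The Primary analysis section fixes the terms of the model for CO-verified abstinence at six months: a mixed-effects logistic regression "with fixed treatment and a random intercept for site". The sensitivity analyses named after it are multiple imputation, last observation carried forward, complete case and as-treated. A Bayesian logistic regression is planned if recruitment falls short. None of these is described as adjusted for a baseline measure.

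The data for adjustment exist. Under Baseline measures: "We will also assess nicotine dependence with the Strength of Urges to Smoke Scale [47] and motivation to quit with the Motivation to Stop Scale". Table 1 schedules both at baseline only. The Randomization section says allocation follows completion of the baseline questionnaire, so both precede it. Blocking there serves to equalize numbers within each site, and no prognostic stratifier is named.

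The opening paragraph of the Analysis section uses baseline characteristics descriptively, by arm. It lists two variables as numeric (most recent diagnosis and acute events) and classes the rest as categorical.

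The Sample size section plans for 616 participants, "with 308 participants asigned to each group", and "with an alpha level of 0.05 in two‐tailed analysis", from two unadjusted proportions.

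**The concern.** Dependence and motivation are plausible predictors of quitting. The Introduction itself links the difficulty this population has in stopping to high nicotine dependence. The eligibility criteria admit people who want to quit, to cut down or to stay abstinent, so motivation may vary widely.

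A primary model that ignores both measures gives up some power. It also leaves no prespecified answer if the baseline table shows the arms to differ on one of them. Adjustment added after that table has been seen is open to the charge of being post hoc, whereas adjustment named in advance is not.

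**Working it through.** **Inputs from the protocol.** 308 per group; two-sided alpha 0.05; main scenario "5% in the control group and 13.1% in the intervention" group, for which the sample "would provide more than 90% power to detect this effect"; conservative scenario "5.0% for the control group vs 11.6% for the treatment group", with 80% power stated.

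**Input assumed.** The odds ratio for abstinence per SD of the baseline covariate. The documents do not give it. The range tried is 1.0 (no association) to 2.7.

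**1. The stated power, without covariates.** Two-proportion formula with pooled variance under the null, where d is the risk difference and p̄ the mean of the two rates:

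power = Φ{[d√n − 1.96√(2p̄(1−p̄))] / √(p₁(1−p₁) + p₂(1−p₂))}

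- 5.0% vs 11.6%, n = 308: [0.066 × 17.55 − 1.96 × 0.3902] / 0.3874 = 1.016, so power is 84.5%.
- 5.0% vs 13.1%, n = 308: [0.081 × 17.55 − 1.96 × 0.4057] / 0.4017 = 1.559, so power is 94.1%.
- With the continuity correction, n is replaced by n(1 − 1/(nd))², which is 278.4 and 283.8. Power becomes 80.8% and 92.2%. The corrected formula needs 303 per group for 80% power in the conservative scenario, close to the planned 308.

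Both stated figures reproduce. The sample size does not rely on adjustment.

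**2. Expected events.** Control: 308 × 0.05 = 15.4. Intervention: 308 × 0.116 = 35.7 or 308 × 0.131 = 40.3. Total: 51.1 to 55.7.

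**3. What a chance imbalance could do.** The 95% limit for the difference in means of a standardized covariate is 1.96 × √(2/308) = 0.158 SD. The shift in the log odds ratio is approximately that difference times the log of the covariate's odds ratio:

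- odds ratio 1.5: 0.158 × 0.405 = 0.064
- odds ratio 2.0: 0.158 × 0.693 = 0.109
- odds ratio 2.5: 0.158 × 0.916 = 0.145

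The planned log odds ratio is 0.91 (conservative) or 1.05 (main). Its unadjusted standard error, √(Σ 1/expected cell count), is 0.316 or 0.311. The shift is therefore 0.064/0.316 = 0.20 to 0.145/0.311 = 0.47 of a standard error.

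**4. What adjustment adds in power.** Logistic regression with and without one normally distributed covariate was fitted to the same simulated trials: 5,000 per scenario, 308 per group, overall rates held at the protocol's values, Wald test. Site effects were left out, in line with the protocol's assumption of negligible clustering.

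| Odds ratio per SD | 5.0% vs 11.6%: unadjusted → adjusted | 5.0% vs 13.1%: unadjusted → adjusted |
|---|---|---|
| 1.0 | 84.3% → 84.3% | 94.4% → 94.4% |
| 1.5 | 85.2% → 85.5% | 94.6% → 94.8% |
| 2.0 | 84.6% → 85.9% | 94.6% → 95.4% |
| 2.5 | 86.0% → 88.3% | 94.4% → 96.0% |

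A separate set of 1,500 runs at 5.0% vs 11.6% gave gains of 0.2, 0.7, 0.8 and 2.3 points at odds ratios of 1.35, 1.65, 2.0 and 2.7.

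Because the overall rates are held fixed, true unadjusted power is the same in every row of a column. Its drift is simulation noise: √(0.85 × 0.15/5000) = 0.5 points per figure. The within-row difference is the quantity to read, since both models see the same data. It runs from 0 to 2.3 points in the conservative scenario and from 0 to 1.6 in the main one.

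**The case against.** The strongest reply is that nothing here is wrong. A logistic model with treatment and site is a legitimate analysis of a randomized trial. Randomization controls type I error, and chance imbalance is already reflected in the standard error. The model matches the unadjusted calculation on which the sample size rests. All of this stands. A reader might infer that the omission biases the comparison or leaves the trial underpowered, but the documents support neither.

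The benefit is also small and rests on an assumed association. The entry criterion on readiness to address smoking may narrow the spread of motivation and push the true value towards the low end of the range. That stands too, and it is why the gain is given as a range starting at zero.

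Nor is adjustment free, or a gain in precision in the usual sense. In a logistic model it moves the target to a conditional odds ratio and usually raises its standard error; what improves is power. If the Analysis section's categorical rule were applied to these scales, each would take one parameter per level beyond the first, with only about 15 events expected in the control arm. These are limits on how the adjustment should be done rather than reasons against it.

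Finally, the statistical analysis plan is not shown and may contain an adjusted analysis, so its absence from a condensed article proves little. But the article does state the terms of the primary model. The proposal replaces that stated choice; it does not fill a gap.

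**Conclusion.** The point holds as an optional improvement of low cost and modest value. The primary model is valid and the stated power is sound, but the model uses no prognostic baseline measure although suitable ones are collected before randomization.

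The expected gain is about 0 to 2 percentage points of power. Prespecification also protects against an imbalance that, even at its 95% limit, would move the log odds ratio by less than half a standard error. The estimates assume an odds ratio per SD of 1.0 to 2.7 for power and 1.5 to 2.5 for the shift. They also assume a covariate that acts linearly on the log odds and negligible site effects. Stronger wording, such as a noticeable distortion of the estimate or an improvement without cost, goes beyond these figures.

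**What to change.** In the Primary analysis section:

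- Add baseline strength of urges to smoke and motivation to stop as prespecified fixed covariates, and keep the random intercept for site.
- Enter each as a single linear score, and state this as an explicit exception to the categorical rule in the Analysis section. Only two parameters are then added against 51 to 56 expected events.
- Report the risk difference and risk ratio standardized over the trial population, so that they stay comparable with the design values (8.1 points and 2.62, or 6.6 points and 2.32).
- Give a simple rule, applied without regard to arm, for a missing baseline score. Such cases should be few, because the baseline questionnaire is completed before allocation.
- Keep the unadjusted model as a sensitivity analysis.

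The cost is a few sentences in the plan, a standardization step and one further model fit. It needs no new data, no change to the sample size and no change to the conduct of the trial. It should be settled before outcome data are examined by arm.

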**Assessments**				
Socio‐demographic characteristics	x			
Nicotine dependence	x			
Motivation to quit	x			
Age started smoking	x			
Smoking duration	x			
Past year quit attempts	x			
Current use of tobacco products other than cigarettes	x			
Ever e‐cigarette use as smoking cessation aid	x			
AUDIT‐C	x			x
Physical activity	x			x
Fruit and vegetable consumption	x			x
Patient Heath Questionnaire‐9	x		x	x
Generalized Anxiety Disorder Scale‐7	x		x	x
7‐day point prevalence			x	x
Sustained abstinence				x
50% smoking reduction			x	x
CO breath sample				x
General mood and physical symptoms			x	x
Adverse events			x	x
Use of e‐cigarette			x	x
Healthcare service use	x		x	x
Health‐related quality of life	x			x

Socio‐demographic characteristics include age, sex, employment status, ethnicity, education, accommodation type and marital status.

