##### Secondary outcomes measures

Continuous abstinence at the 6‐month follow‐up, defined as not having had more than five cigarettes in the period from 2 weeks after baseline to the follow‐up, in line with the Russell Standard [40]. Self‐reported smoking abstinence at 2–4 weeks from baseline or target quit date (whichever is later). Fifty percent smoking reduction at 1‐ and 6‐month follow‐ups, calculated by the reduction in self‐reported cigarettes per day from baseline. Number of unsuccessful quit attempts at the 1‐ and 6‐month follow‐ups.

Mental health symptoms assessed by Patient Health Questionnaire‐9 (PHQ‐9) [43] and General Anxiety Disorder‐7 (GAD‐7) [44], general mood, physical symptoms assessed by the Mood and Physical Symptoms Scale (MPPS) [45, 46], and experience of adverse events at the 1‐ and 6‐month follow‐ups, similar to previous research [23].

Cost‐effectiveness of the intervention based on health economics measures outlined below.

The fidelity of intervention implementation and satisfaction with the intervention at the 1‐ and 6‐month follow‐ups will be based on questions related to e‐cigarette use in the past month as well as a question to assess whether the e‐cigarette used in the last month was the device provided to intervention participants as part of the study.

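### PHQ-9 and GAD-7 each have two unranked treatment-effect estimates, and neither uses the baseline score as a covariate

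*Protocol article*

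**What the plan says.** Table 1 of the protocol article lists "Patient Heath Questionnaire‐9" and "Generalized Anxiety Disorder Scale‐7" at baseline, 1 month and 6 months. The secondary outcomes section begins the relevant entry with "Mental health symptoms assessed by Patient Health Questionnaire‐9 (PHQ‐9", adds GAD-7, and places both at the two follow-ups. The secondary objectives name only the 6-month follow-up for mental health outcomes.

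The section headed Primary analysis then covers these scores twice.

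- **General rule for secondary outcomes.** Binary outcomes follow the primary model, a "logistic regression model with fixed treatment and a random intercept for site". Continuous outcomes are analysed "or with mixed effects (multilevel) linear regression adjusting for site‐level variation if they are continuous numeric variables", and "Mean difference will be reported". Site is the only adjustment named.
- **Repeated-measures rule.** A further model examines "mental health symptoms across baseline, and the 1‐and 6‐month follow‐ups". It has fixed effects for group, categorical time and their interaction, and random intercepts for participant and site. Baseline is one of the outcome time points.

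The text does not say which of the two gives the reported treatment effect. The Analysis section, after describing how baseline characteristics will be summarised, adds: "Numeric variables include most recent diagnosis and acute events. All other variables are treated as categorical".

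**The concern.** A baseline value of the same scale is usually the strongest available predictor of the follow-up value. Entering it as a covariate is free once it has been collected. Here it is collected, yet it is a covariate in neither model.

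The two models also answer the question with different contrasts. The first compares arms at follow-up and ignores where they started. The second compares change from baseline. If the arms differ by chance at baseline, the two results diverge, and a reader of the final report could not tell which was pre-specified. The Bayes factor rule, which applies when the primary and other outcomes are non-significant, has the same difficulty: with two tests per score it is unclear which one triggers it.

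The introduction stresses that earlier studies found no adverse mental health effect of e-cigarettes. One clear and reasonably precise estimate per score therefore has practical value.

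**Working it through.** **Inputs.** From the Sample size section: 308 per arm, two-sided alpha 0.05. The article gives no SD, no correlation and no precision or power figure for PHQ-9 or GAD-7, so there is no stated figure to reproduce for these scores. As a check on the design inputs, the stated power for the primary outcome does reproduce: 5% v 13.1% gives 94.1% (stated as more than 90%), and 5.0% v 11.6% gives 80.8% with continuity correction (stated as 80%; 84.5% without).

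**Assumptions.** Baseline to 6-month correlation r of 0.3, 0.5 and 0.7; equal variance at the two times; complete data. Results are in units of the score's SD.

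**Formulas for the standard error (SE) of the 6-month contrast.**

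- Follow-up only: √(2/n) = √(2/308) = 0.0806
- Difference in change: 0.0806 × √(2(1−r))
- Baseline-adjusted: 0.0806 × √(1−r²)
- Adjusted relative to change: √((1−r²)/(2(1−r))) = √((1+r)/2)

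| | r = 0.3 | r = 0.5 | r = 0.7 |
|---|---|---|---|
| SE, follow-up only | 0.0806 | 0.0806 | 0.0806 |
| SE, difference in change | 0.0953 | 0.0806 | 0.0624 |
| SE, baseline-adjusted | 0.0769 | 0.0698 | 0.0575 |
| SE cut v follow-up only | 5% | 13% | 29% |
| SE cut v difference in change | 19% | 13% | 8% |
| Equivalent sample v follow-up only, 1/(1−r²) | 1.10 | 1.33 | 1.96 |
| Equivalent sample v change, 2/(1+r) | 1.54 | 1.33 | 1.18 |

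For any r between 0 and 1 the adjusted SE is below both others. Below r = 0.5 the change contrast is less precise than the raw comparison. If only 80% in each arm give a score, every SE rises by 1/√0.8 = 1.12 and the ratios stay the same.

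**How far the two planned estimates can diverge.** With complete data the group-by-time term at 6 months equals the follow-up difference minus the baseline difference. The gap between the two planned results is therefore the chance baseline difference, which has SE 0.081 SD at 308 per arm. A fitted random-intercept model on one simulated trial (SD 6 points) confirmed this: the interaction was 0.793 and the baseline difference −0.707, which sum to 0.086, the follow-up difference.

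The correlation between the two estimates is √((1−r)/2), or 0.59, 0.50 and 0.39 at r = 0.3, 0.5 and 0.7. With no true effect and r = 0.5, they had opposite signs in 32% of 4,000 simulated trials. Theory gives arccos(0.5)/π = 33%.

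**Illustration.** For an assumed true difference of 0.2 SD with complete data, power is 70% for follow-up only. It is 56%, 70% and 89% for the change contrast, and 74%, 82% and 94% with adjustment, at r = 0.3, 0.5 and 0.7.

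**The case against.** The strongest reply is that baseline is used. The repeated-measures model is written specifically for mental health scores and its contrast is change from baseline, so it takes the baseline difference into account. The general rule has to cover outcomes such as the mood and physical symptoms scale, which Table 1 does not schedule at baseline. A specific rule following a general one may be read as governing, and the objectives already point to 6 months. An article may also leave the choice of principal model to an analysis plan.

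Much of this stands. A reader might infer that the baseline scores are ignored or that the results would be biased. The text does not support either reading: the second model uses them, and under randomization both estimates are unbiased. Nor does the 29% cut, or near-doubling of the effective sample, describe the plan as a whole. That figure applies only against the follow-up comparison at r = 0.7; against the change contrast the gain there is 8%.

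It is also tempting to say that the plan treats PHQ-9 and GAD-7 as categorical. The typing sentence follows the text on describing baseline characteristics, and the Primary analysis section calls the mental health scores continuous. Finally, the article states no margin or formal no-harm test for these scores, so a failure to demonstrate safety cannot be alleged.

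What the reply does not remove is that both models are written into the article, both reach these scores, neither is ranked, and neither has the baseline score as a covariate. The objection that details are left to an analysis plan does not apply to models the article itself specifies.

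**Conclusion.** The point holds as a matter of precision and clarity for two secondary outcomes. The SE gain from adjustment is modest to substantial depending on r: about 5% to 29% against the follow-up comparison and 19% to 8% against the change contrast as r goes from 0.3 to 0.7. These figures rest on an assumed correlation, equal variances and complete data. The conclusion that adjustment beats both planned estimates does not depend on which r between 0 and 1 applies. The lack of ranking is a fact of the text and needs no assumption.

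The change is worth making but not critical. The typing of variables in the Analysis section is a separate, smaller wording error: diagnosis is not a numeric quantity, and Table 2 records age in years from 18 to 99.

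**What to change.** For PHQ-9 and GAD-7 only, replace the two analyses with one mixed model per score:

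- outcomes: the 1- and 6-month scores;
- fixed effects: baseline score as a continuous covariate, group, time and group-by-time;
- random intercepts: participant and site.

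An acceptable alternative is to keep the existing repeated-measures model and constrain the baseline means to be equal between arms. In either case, name the 6-month between-arm contrast as the reported estimate, and use it wherever a later rule depends on the result for that score.

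Keep the follow-up-only model for the mood and physical symptoms scale.

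Separately, reword the Analysis sentence so that diagnosis is described as categorical and age and other numeric measures as numeric.

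The cost is wording only. All the data are already scheduled, and the sample size and primary analysis do not change. The revision should be made before unblinded data are seen.

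### The repeated-measures logistic model for ≥50% smoking reduction includes baseline, where the outcome is 0 for everyone, so its baseline-referenced terms have no finite estimate; its overdispersion check and negative binomial fallback do not suit a binary outcome

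*Protocol article*

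**What the plan says.** The Primary analysis section of the protocol article describes one repeated-measures analysis for two kinds of outcome. It is to examine "changes in cigarette consumption (a reduction of ≥50%) and mental health symptoms across baseline", and the sentence goes on to name the 1- and 6-month follow-ups. On the smoking outcome it states: "For the binary outcome of a ≥50% reduction in cigarette consumption, we will use a mixed‐effects logistic regression model". It then checks residual deviance against degrees of freedom and "will consider alternative models, such as negative binomial regression, if overdispersion is present". One specification serves both kinds of outcome: "fixed effects for the intervention group, time (treated as a categorical factor) and their interaction to assess differential changes between groups over time". On clustering, "we will include random intercepts for each participant and clinic site".

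Two other places define the reduction outcome. Under Secondary outcomes measures it is "calculated by the reduction in self‐reported cigarettes per day from baseline". In Table 1 the row "50% smoking reduction" is marked at 1 month and 6 months and is blank at baseline.

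**The concern.** A reduction measured from baseline is 0% at baseline, so the yes/no outcome is 0 for every participant in both arms at that time. If baseline is one of three levels of categorical time, two of the six group-by-time cells contain only zeros. The logistic likelihood then pushes the fitted log odds in those cells towards minus infinity (quasi-complete separation). The terms expressed against baseline include the group-by-time interactions that are meant to show differential change between arms. Their printed values would depend on software settings, not on the data.

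Separately, the overdispersion rule is stated for an outcome that the paragraph has just called binary. An analyst who followed it could be led to a count model for a yes/no result.

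**Working it through.** The plan gives no numerical result for this model and no expected rate for ≥50% reduction, so there is no figure to reproduce. The check is algebra plus one simulated illustration.

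**1. Which terms are estimable**

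Write the log odds as b0 + b1·group + b2·(1 month) + b3·(6 months) + b4·group×(1 month) + b5·group×(6 months).

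- Baseline cells: b0 (control) and b0 + b1 (intervention). Every outcome is 0, so the likelihood rises without limit as both go to minus infinity.
- Consequence: b0 diverges, and b2 and b3 diverge upwards to compensate. b1 is the difference of two unbounded quantities and is not identified, so b4 and b5 are not identified either.
- Estimable: the arm contrast at 1 month, b1 + b4; at 6 months, b1 + b5; and the 6- versus 1-month interaction, b5 − b4. The baseline log odds cancel from all three.

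**2. Illustration**

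Input from the protocol: 308 per arm (Sample size). Assumed, because the document gives no rates for this outcome: log odds −1.2 (1 month) and −1.5 (6 months), group effect 0.7, participant random-intercept SD 1.5. Simulated rates, control versus intervention: 0% and 0% at baseline, 29.5% and 41.6% at 1 month, 24.0% and 39.6% at 6 months.

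*Fixed-effects logistic model, three time points:*

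| Iterations | b0 | b2 | SE of b0 | SE of b1 | Deviance |
|---|---|---|---|---|---|
| 5 | −6.564 | 5.695 | 0.92 | 1.30 | 1547.015 |
| 15 | −16.566 | 15.697 | 136.73 | 193.36 | 1545.279 |
| 25 | −26.566 | 25.697 | 20,292 | 28,697 | 1545.279 |

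The intercept falls by about 1 per iteration while the deviance stops changing. At 25 iterations the SEs of b2 and b3 are also 20,292, and those of b4 and b5 are 28,697.

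For comparison, the 1-month arm contrast taken directly from the simulated counts (91/308 and 128/308) has SE = √(1/91 + 1/217 + 1/128 + 1/180) = √0.02897 = 0.17.

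*Participant random-intercept logistic model (25-point quadrature):*

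| Fit | b0 | b1 | b4 | b5 | b1+b4 | b1+b5 | b5−b4 | −log likelihood |
|---|---|---|---|---|---|---|---|---|
| 3 times, tolerance 0.1 | −10.81 | 0.24 | 0.43 | 0.68 | 0.670 | 0.918 | 0.248 | 760.112 |
| 3 times, tolerance 0.001 | −17.25 | 0.60 | 0.07 | 0.31 | 0.670 | 0.918 | 0.248 | 760.084 |
| 3 times, tolerance 0.00001 | −18.49 | 0.67 | 0.00 | 0.25 | 0.670 | 0.918 | 0.248 | 760.084 |
| 1 and 6 months only | – | – | – | – | 0.670 | 0.918 | 0.248 | 760.084 |

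The 1-month interaction against baseline moves from 0.43 to 0.00 for a log-likelihood change of about 0.03. The three baseline-free contrasts do not move and equal the follow-up-only fit. The baseline rows add no information.

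**3. The overdispersion check**

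For a single 0/1 observation with probability p, expected deviance is −2[p ln p + (1−p) ln(1−p)]. At p = 0.30 this is −2[0.30×(−1.204) + 0.70×(−0.357)] = 1.22.

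| p | 0.05 | 0.10 | 0.20 | 0.30 | 0.50 |
|---|---|---|---|---|---|
| Expected deviance | 0.40 | 0.65 | 1.00 | 1.22 | 1.39 |

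None of these cases has any overdispersion. The ratio tracks the event rate and passes 1 at about 20%.

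**4. The negative binomial alternative**

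Negative binomial variance is at least the mean μ. Binary variance is μ(1−μ), always below μ. The simulated follow-up data agree: the Poisson Pearson statistic over df is 0.66 (average rate 0.337, and 1 − 0.337 = 0.663), and the fitted negative binomial dispersion is about 0.000001. The fallback collapses to a Poisson model for a yes/no outcome.

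**The case against.** The strongest defence is that the wording is merely loose. One sentence covers two outcomes, baseline is a proper time point for the symptom scores, and Table 1 leaves no baseline value of the reduction outcome to enter. That may be what was intended, but the text names baseline for both outcomes and applies one time factor to both models. Table 1 therefore shows an inconsistency to settle and does not settle it.

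Other parts of the defence stand:

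- A reader might infer that the intervention effect on smoking reduction cannot be estimated at all. It can. The contrasts at 1 and 6 months and their difference are recoverable even from the model as written. The same section also analyses binary secondary outcomes at each follow-up with a mixed logistic model that has no baseline row.
- A reader might treat this as the trial's main harm-reduction analysis. The document gives it no such status; it is an additional longitudinal analysis of a secondary outcome.
- The text only says that alternatives will be considered, so no one is bound to a count model.
- The large standard errors depend on the iteration limit and on assumed rates. They show non-existence of the estimate and do not measure harm.

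Two further inferences are not supported. Baseline cigarettes per day has no row in Table 1, but the outcome definition implies that it is collected, and a condensed article need not list every item. "Number of unsuccessful quit attempts" is a count outcome for which the article names no specific model; that choice can properly sit in the analysis plan, which is not shown.

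**Conclusion.** Wrong as written, and it should be corrected, but the reach is limited. In the repeated-measures logistic model for ≥50% reduction, the intercept, the baseline group effect, and the time and interaction terms against baseline have no finite maximum-likelihood estimate. This follows from the outcome's definition and holds whatever the follow-up rates are. The deviance check and the negative binomial alternative do not apply to this outcome; that too is independent of the assumed rates.

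The coefficients and standard errors shown rest on one simulated data set with assumed rates. The simulation omitted the site random intercept, which does not alter the all-zero baseline cells. The primary outcome, the by-visit secondary analyses and the repeated-measures models for PHQ-9 and GAD-7 are not affected by the baseline problem.

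**What to change.** - State that baseline is a level of time for PHQ-9 and GAD-7 only.
- Fit the ≥50% reduction model to 1 and 6 months, with group, time, group × time, and random intercepts for participant and site. Report the group contrast at each time.
- Delete the overdispersion and negative binomial sentence for this outcome.

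The cost is a change of analysis wording. No data collection, sample size or trial procedure changes. It is best made before outcome data are seen by arm, so that the model is not chosen after a failed fit.
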